## Abstract

**Background:**

There is growing recognition of a syndrome of disturbed grief referred to as prolonged grief disorder (PGD). PGD is mostly studied in adults, but clinically significant PGD symptoms have also been observed in children and adolescents. Yet, to date no effective treatment for childhood PGD exists. The aims of this study are: (1) to investigate the effectiveness of *Grief-Help*, a nine-session cognitive-behavioural treatment for childhood PGD, combined with five sessions of parental counselling, immediately after the treatment and at three, six and twelve months follow-up; (2) to examine tentative mediators of the effects of *Grief-Help,* (i.e., maladaptive cognitions and behaviours and positive parenting), and (3) to determine whether demographic variables, child personality, as well as symptoms of PGD, anxiety, and depression in parents moderate the treatment effectiveness.

**Methods/Design:**

We will conduct a Randomised Controlled Trial (RCT) in which 160 children and adolescents aged 8–18 years are randomly allocated to cognitive behavioural *Grief-Help* or to a *supportive counselling* intervention; both treatments are combined with five sessions of parental counselling. We will recruit participants from clinics for mental health in the Netherlands. The primary outcome measure will be the severity of Prolonged Grief Disorder symptoms according to the Inventory of Prolonged Grief for Children (IPG-C). Secondary outcomes will include PTSD, depression and parent-rated internalizing and externalizing problems. Mediators like positive parenting and maladaptive cognitions and behaviours will be identified. We will also examine possible moderators including demographic variables (e.g. time since loss, cause of death), psychopathology symptoms in parents (PGD, anxiety and depression) and child personality. Assessments will take place in both groups at baseline, after the treatment-phase and three, six and twelve months after the post-treatment assessment.

**Discussion:**

We aim to contribute to the improvement of mental health care for children and adolescents suffering from loss. By comparing *Grief-Help* with *supportive counselling*, and by investigating mediators and moderators of its effectiveness we hope to provide new insights in the effects of interventions for bereaved children, and their mechanisms of change.

**Trial registration:**

Netherlands Trial Register NTR3854

## Background

The death of a loved one in childhood and adolescence is associated with increased emotional problems, including elevated depression, anxiety and posttraumatic stress, as well as somatic complaints and behavioural problems [1,2]. From among all children who experience such a loss, an estimated 5% to 10% go on to experience clinically significant psychiatric problems. Such problems include major depression, posttraumatic stress disorder (PTSD) and prolonged grief disorder (PGD) [3,4].

PGD encompasses several symptoms, including separation distress, preoccupation with thoughts about the lost person, a sense of purposelessness about the future, numbness, bitterness, difficulty accepting the loss and difficulty moving on with life without the lost person [5,6]. Empirical studies have shown that PGD symptoms can be reliably assessed in children and adolescents [7]. PGD symptoms can be distinguished from normal grief, depression and anxiety, including PTSD, and are associated with significant concomitant internalizing and externalizing problems [7-10].

Few effective interventions for bereaved children and adolescents are available. On the basis of a meta-analysis of 13 controlled studies examining the effectiveness of bereavement interventions with children, Currier *et al*. [11] concluded that interventions available at the time were not more useful than undergoing no intervention. Indeed, a number of controlled studies have been conducted on the treatment of bereaved children, including studies examining family interventions for bereaved children [12], music therapy in groups [13], group therapy for children [14] and group therapy for children bereaved by the suicide of a relative [15]. These studies are limited by the fact that they did not articulate the theoretical basis of the intervention tested [11], focused on generic indices of distress rather than on symptoms of grief [12,15] or did not randomly allocate participants to treatment and control groups [13,14].

In the past decade, several promising lines of research have greatly advanced our understanding of bereavement interventions for children. The first and most extensive line of research concerns the family bereavement program (FBP), developed by Sandler and colleagues [16,17]. The FBP is a group-based program that targets family-level variables (for example, parenting skills) and child-level variables (for example, coping skills) that promote resilience. The FBP was found to reduce immediate and long-term emotional problems in children confronted with parental loss. A second promising intervention is the trauma and grief component therapy (TGCT) developed by Layne *et al*. [18]. TGCT is a group treatment for adolescents confronted with loss in the context of a civil war. This treatment proved to be effective in terms of reducing grief, depression and anxiety symptoms [2,18]. A third important line of research concerns the work of Cohen and colleagues [19,20] on cognitive-behavioural therapy for childhood traumatic grief (CBT-CTG). This treatment approach explicitly focuses on the alleviation of the emotional condition termed *childhood traumatic grief*, which is defined as a combination of traumatic and grief stress reaction, among children exposed to deaths that occurred under traumatic circumstances (for example, motor vehicle accidents, suicide, homicide). Two uncontrolled studies showed that children who underwent CBT-CTG reported significant improvement in CTG and PTSD symptoms [19,20].

Notwithstanding the importance of these three research lines, they still leave room for further study and refinement of treatment options for children confronted with the death of a loved one. For instance, the FBP and TGCT are limited to a group-based format, which may yield practical problems; for example, clients may have to wait until there are enough children for a group and may be less effective because it is less well-adjusted to an individual child’s circumstances. In addition, all three approaches are limited by their focus on restricted groups, such as parentally bereaved children (FBP) or children exposed to traumatic deaths (TGCT and CBT-CTG), making these approaches less suitable for use with other groups of bereaved children. The impact of these treatments on PGD symptoms, as currently defined [5,6], is unknown.

Given the need for effective therapy for PGD symptoms in children and adolescents, we developed a nine-session protocolized cognitive-behavioural treatment that is administered in combination with five sessions of parental counselling. This treatment is called *Grief-Help*. It is based on a cognitive-behavioural model of processes that interfere with adjustment to loss. Two pilot studies of this treatment have been done.

The first was a multiple-baseline study of six bereaved children and adolescents, which showed that the intervention coincided with reductions in symptoms of PGD, depression, PTSD and (parent-rated) internalizing and externalizing problems [21]. The intervention proved to be feasible, as both children and parents evaluated the treatment positively. That is, all participating children and parents gave favourable scores regarding their satisfaction with each session, the contact with their therapist and the information they received, attesting to the feasibility of this treatment approach. Results showed that after treatment there were reductions in symptoms of PGD, depression, posttraumatic stress and parent-rated internalizing and externalizing problems. Averaged across the six participants, reductions in scores on the outcome measures were all statistically significant, and all pretreatment to posttreatment effect sizes were large (Cohen’s *d* > 0.8).

The second pilot study was an open trial conducted with ten children and adolescents [22]. We conducted this study to evaluate the potential effectiveness of Grief-Help therapy among children confronted with losses other than the loss of a parent or sibling and to investigate whether the program is effective when the loss occurred more than 12 months prior to initiation of treatment. In this study, patients significantly improved from pretreatment to posttreatment, with large improvements observed in self-rated PGD and bereavement-related posttraumatic stress (effect size (ES) > 0.8) and small to moderate improvements in depression and parent-rated internalizing and externalizing problems (0.2 < ES < 0.8). Additional analyses focused on predictors of treatment outcomes suggested that Grief-Help therapy might be less effective for children and adolescents who are further removed in time from the loss and for those confronted with loss due to suicide. Taken together, Grief-Help therapy appears to be a promising treatment, and controlled evaluation is clearly indicated.

### Trial objective

This randomised controlled trial seeks to examine the effect of cognitive-behavioural Grief-Help therapy for children with emotional problems following the death of a loved one. Participants are randomly assigned to one of two treatment conditions: (1) cognitive-behavioural Grief-Help therapy combined with parental support or (2) a control treatment consisting of nondirective supportive counselling combined with parental support. Participants are asked to complete questionnaires before and after treatment and at three follow-up assessment points.

This treatment trail has three goals. First, we want to compare the effects of cognitive behavioural Grief-Help therapy with the effects of supportive counselling by measuring the reduction of PGD symptoms and other emotional problems, including depression and PTSD. Our second goal is to gain knowledge about variables that are expected to mediate the effects of Grief-Help therapy, such as maladaptive cognition, avoidance behaviours and positive parenting (warmth, involvement and autonomy-granting). We also want to generate knowledge about variables that moderate the effectiveness of Grief-Help therapy.

We hypothesize that the Grief-Help group will show a greater reduction of PGD symptoms and other emotional problems (for example, depression, PTSD symptoms) than the supportive counselling group immediately after treatment and at each follow-up point (three, six and twelve months later). Furthermore, we expect that this reduction will be mediated by a change in maladaptive cognitions and behaviours as well as by increases in positive parenting. We consider the following factors to be possible moderators: demographic variables, severity of symptoms before treatment, time since loss, cause of death, child personality and psychopathology symptoms in parents. We will use state-of-the art statistical techniques to analyse temporality, causality and mechanisms of change.

## Method/Design

### Study design

We will conduct a randomised controlled trial with two intervention groups: Grief-Help therapy versus supportive counselling (Figure 1). Ethical approval was granted by an independent medical ethics committee (Central Committee on Research Involving Human Subjects NL30528.041.09).

**Figure 1 F1:**
[figure not shown]
Diagram showing flow of participants through the study.

### Participants

Participants will be bereaved children and adolescents (and their parents) who apply for help in outpatient mental health care clinics in The Netherlands. The following inclusion criteria will be used: (1) ages 8 through 18 years, (2) loss of a close relative, (3) symptoms of PGD as the primary problem and reason for seeking therapy, (4) absence of mental retardation, (5) absence of severe conduct disorder and developmental disorders, (6) no concurrent psychological or psychopharmacological treatment and (7) no current substance abuse or dependence, no psychotic symptoms and no severe depression with risk of suicide in participating children or their parents.

### Procedure and randomisation

Potentially eligible participants (and their parents) referred to the participating clinics by their general practitioners will receive oral and written information about the research program. Surviving parents’ consent will be obtained for their children to participate. Assent or consent will be obtained from the children, depending on their age. Children will then complete baseline measures (assessment 1 (A1)) in the presence of a therapist. Parents will also complete baseline measures at A1.

Randomisation will take place after informed consent is obtained and after completion of the baseline measures (A1). Participants will be randomly allocated to one of two treatment conditions. Both treatments will be introduced to participants as potentially useful interventions for bereaved children. Four follow-up assessments will be conducted: directly after completion of the treatment (A2) and three, six and twelve months later (A3, A4 and A5, respectively).

### Measures

All measures, time points and informants are summarized in the assessment schedule (Table 1).

**Table 1 T1:** **Assessment schedule**^**a**^

**Variable**	**Concept**	**Measure**	**Informant**	**Assessment**	**Goal**
Primary outcome measure	PGD symptoms	IPG-C	Child	A1, A2, A3, A4, A5	1, 2, 3
Secondary outcome measures	PTSS symptoms	CPSS	Parent	A1, A2, A3, A4, A5	1, 2, 3
	Depression symptoms	CDI	Child	A1, A2, A3, A4, A5	1, 2, 3
	Behaviour problems	CBCL	Child	A1, A2, A3, A4, A5	1, 2, 3
Mediator	Positive parenting	PPQ, MFP	Parent and child	A1, A2, A3, A4, A5	2
	Maladaptive cognitions and behaviours	GCQ-C-II, GBQ-C-II	Child	A1, A2, A3, A4, A5	2
Moderator	Demographic variables	Demographic questions	Parent and child	A1	3
	PGD symptoms (parents)	ICG-R	Parent	A1	3
	Anxiety and depression (parents)	HADS	Parent	A1	3
	Child personality	H*i*PIC	Parent	A1	3

^a^CBCL = Child Behavior Checklist, CDI = Children’s Depression Inventory, CPSS = Child Posttraumatic Stress Disorder Symptom Scale, GBQ-C = Grief Behavior Questionnaire for Children, GCI-C = Grief Cognition Questionnaire for Children, HADS = Hospital Anxiety and Depression Scale, H*i*PIC = Hierarchical Personality Inventory for Children, ICG-R = Inventory of Prolonged Grief–Revised, IPG-C = Inventory of Prolonged Grief for Children, MFP = Mother-Father-Peer Scale, PPQ = Parenting Practices Questionnaire.

### Primary outcome measure

#### Inventory of prolonged grief for children

The Inventory of Prolonged Grief for Children (IPG-C) is a 30-item measure of PGD symptoms. It is an adapted version of the Inventory of Complicated Grief developed to assess adult PGD [23] that taps all symptoms listed in the PGD criteria proposed for the *Diagnostic and Statistical Manual of Mental Disorders, Fifth Edition* (DSM-5),and the *International Classification of Diseases, 11th Revision* (ICD-11) [5], as well as several additional markers of dysfunctional grief. The IPG-C rates symptom frequency in the past month on three-point scales ranging from 1 (almost never) to 3 (always). The measure has good internal consistency, stability and concurrent validity (for example, high correlations with other measures of grief) [10].

### Secondary outcome measures

#### Child PTSD symptom scale

The Child PTSD Symptom Scale (CPSS) is a 17-item questionnaire for the assessment of PTSD symptoms, as defined in the DSM-IV, constructed by Foa *et al*. [24]. Respondents rate the occurrence of symptoms on four-point scales ranging from 0 (not at all/only once a week) to 3 (almost always/five or more times a week). The index event is defined as “the death of your loved one”. Research has shown that the CPSS has good reliability and convergent and discriminant validity [24-26].

#### Children’s depression inventory

The Children’s Depression Inventory (CDI) is a well-validated 27-item measure of depression symptoms [27-29]. Each item contains three statements representing depressive symptoms at increasing levels of severity, from among which respondents select the one statement that best describes how he or she felt during the preceding week.

#### Child behavior checklist

The Child Behavior Checklist (CBCL) [30] is a 118-item measure of emotional and behavioural problems of children 6 to 18 years of age that is completed by parents. Items are rated on three-point scales with the anchors being 0 (not true) and 2 (very true/often true). Scores can be used to obtain indices of internalizing problems and externalizing problems. The summed score of all items represents a Total Problem score. The psychometric properties of the original version [30] and Dutch version [31] are adequate.

### Potential mediators

#### Positive parenting

##### Parenting practices questionnaire

Two scales of the Parenting Practices Questionnaire (PPQ) [32] are used: warmth and involvement (11 items) and reasoning/induction (7 items). According to Locke and Prinz [33], the PPQ has adequate psychometric characteristics. The items are rated on a five-point scale ranging from 1 (never) to 5 (always).

##### Mother-father-peer scale

The Mother-Father-Peer Scale (MFP) is administered to assess psychological autonomy-granting, an aspect of positive parenting [34]. Only the mother and father parts of the scale are included. Because of time constraints, a slightly shorter version of the scale from the original inventory will be used (nine of the original thirteen items). Using a Likert scale ranging from 1 (not at all) to 5 (very much), each of the parents fills out the scales with regard to his or her relationship with their child. The inventory has good reliability and has been validated against several other measures of parenting [35].

### Maladaptive cognitions and behaviours

#### Grief cognition questionnaire for children

The Grief Cognition Questionnaire for Children (GCQ-C) is a 20-item measure of maladaptive grief cognitions and is based on the Grief Cognitions Questionnaire for adults [36]. The CGQ-C rates the frequency of maladaptive cognitions during the past 2 weeks on four-point scales ranging from 1 (never) to 4 (very often). The internal consistency, temporal stability and concurrent and construct validity of the questionnaire are adequate ([name], [name] and [name], unpublished observations).

#### Grief behaviour questionnaire for children

The Grief Behaviour Questionnaire for Children (GBQ-C) was specifically designed for this study to assess strategies to avoid confrontation with the reality of the loss (called “anxious avoidance”) and a tendency to refrain from activities that could foster adjustment (called “depressive avoidance”). Its 12 items are based on items from the Depressive and Anxious Avoidance in Prolonged Grief Questionnaire (DAAPGQ) developed by [name], Van den Bout and colleagues [37,38].

### Potential moderators

#### Hospital anxiety and depression scale

The Hospital Anxiety and Depression Scale (HADS) [39] is a 14-item measure of anxiety and depression symptoms in adults. The Dutch version of the HADS has been validated [40]. Items are rated on a four-point Likert scale, with higher ratings indicating higher states of anxiety or depression.

#### Inventory of complicated grief–revised

The Inventory of Complicated Grief–Revised (ICG-R) was developed by Prigerson and Jacobs [23] as a 30-item measure of PGD symptoms in adults. The Dutch version of the measure has good internal consistency, stability and concurrent validity [41]. Respondents rate the occurrence of these symptoms during the past month on five-point scales ranging from “never” to “all the time”.

#### Hierarchical personality inventory for children

The Hierarchical Personality Inventory for Children (H*i*PIC) is a 144-item personality inventory that assesses individual differences between children within the framework of the Big Five, which is completed by parents. Dimensions that can be identified are extraversion (32 items), benevolence (40 items), conscientiousness (32 items), emotional stability (16 items) and imagination (24 items). It has been shown to have high convergent and discriminant validity as well as temporal stability [42,43]. The items are scored on a five-point scale, ranging from 1 (hardly characteristic) to 5 (very characteristic).

### Other information

Demographic information will be assessed at baseline. Treatment adherence will be measured in terms of the number of sessions attended and completion of homework assignments. Adherence to both treatment protocols will be promoted by regular meetings with the therapist. Therapy sessions will be audiotaped, and randomly selected tapes will be discussed to ensure that therapists adhere to the protocols.

### Sample size

Our sample size calculation is based on the conventional significance (α) and power (1 – β) levels of 0.05 and 0.80, respectively, planning one-sided testing. The sample size of this study is based on the expected difference on the primary outcome variable (that is, PGD symptoms) between the two conditions. On the basis of a power of 0.80, an α of 0.05 and an expected dropout percentage of 20%, we will need 80 participants for each condition to show an effect size of 0.50 [44]. Therefore, we have determined the total sample size to be 160.

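### The sample size is declared for one-sided testing, but 80 per condition is what the stated inputs give for a two-sided test; sidedness, power and N do not agree

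*Protocol article*

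**What the plan says.** The Sample size section of the protocol article rests the calculation on "conventional significance (α) and power (1 – β) levels of 0.05 and 0.80, respectively", and adds "planning one-sided testing". It ties the calculation to the expected difference between conditions in PGD symptoms, the primary outcome. With "an expected dropout percentage of 20" per cent, it concludes that "we will need 80 participants for each condition to show an effect size of 0.50", and so "we have determined the total sample size to be 160".

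Two other sections bear on the point. Under Trial objective the hypothesis is directional: Grief-Help is expected to reduce symptoms more than supportive counselling. Under Statistical analyses the outcomes are to be compared by analysis of covariance with the pre-intervention score as covariate. That section does not say whether the tests are one-sided or two-sided.

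**The concern.** An effect size of 0.50 with 64 analysed per group is a familiar pairing, and it belongs to a two-sided test at 0.05 with 80% power. Finding it, inflated for 20% dropout, beside a declaration of one-sided testing suggests that the declared test and the number come from different calculations.

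The stake is the decision rule for the primary outcome, not the number of children. A one-sided test at 0.05 accepts a 5% chance of a false claim for Grief-Help. A two-sided test at 0.05 accepts 2.5% in that direction and also allows a formal finding in favour of supportive counselling, which is an active treatment with the same number of sessions. Because the Sample size section points both ways and the analysis section is silent, a result between the two thresholds could be called positive or not depending on which part of the paragraph is followed.

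**Working it through.** **Inputs, all from the Sample size section:** standardised difference d = 0.50, alpha = 0.05, power = 0.80, dropout 20%, equal allocation. Stated result: 80 per condition, 160 in total.

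**Formula.** For two means with equal groups, the normal approximation is n per group = 2(z_α + z_β)² / d², with z_β = 0.8416 for 80% power. The exact figure comes from the noncentral t distribution with 2n − 2 degrees of freedom. The number to randomise is n / (1 − 0.20).

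**Reproducing the stated 80 (two-sided 0.05, z = 1.9600).**
- Normal approximation: 2 × (1.9600 + 0.8416)² / 0.25 = 62.8, so 63.
- Noncentral t: 63.8, so 64 analysed.
- Dropout: 64 / 0.8 = 80 per condition, 160 in total. The stated figure is reproduced exactly. (The normal approximation gives 63 / 0.8 = 78.75, so 79.)

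**The test actually named (one-sided 0.05, z = 1.6449).**
- Normal approximation: 2 × (1.6449 + 0.8416)² / 0.25 = 49.5, so 50.
- Noncentral t: 50.2, so 51 analysed.
- Dropout: 51 / 0.8 = 63.75, so 64 per condition, 128 in total. (The normal approximation gives 63.)
- Inflating by multiplication instead, 51 × 1.2 = 61.2, so 62, is no closer to 80.

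The stated total exceeds the one-sided requirement by 160 / 128 − 1 = 25%.

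**Power with 64 analysed per condition (80 × 0.8), d = 0.50, unadjusted t-test.**

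| Test at 0.05 | Power | Effect detectable at 80% power |
|---|---|---|
| One-sided | 0.879 | 0.44 |
| Two-sided | 0.801 | 0.50 |

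**Effect of the planned ANCOVA.** Adjusting for the baseline score multiplies the residual variance by 1 − r², where r is the correlation between baseline and outcome, so d is replaced by 0.50 / √(1 − r²). The article gives no r. Assuming r between 0.3 and 0.7, power with 64 per condition is about 0.84 to 0.98 two-sided and 0.90 to 0.99 one-sided. Adjustment therefore lowers the N required and cannot explain a number that is larger than the one-sided calculation needs.

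**Where the two rules part.** With 64 per condition the test has 126 degrees of freedom, and the smallest significant observed d is t_crit × √(2/64).
- One-sided: 1.657 × 0.1768 = 0.29.
- Two-sided: 1.979 × 0.1768 = 0.35.

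An observed standardised difference between about 0.29 and 0.35 (unadjusted) is significant under one rule and not under the other.

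**The case against.** The strongest reply is that the number errs on the safe side. With 160 children, power reaches at least 80% under either sidedness, and more with the planned covariate. That stands: neither power nor recruitment is harmed, and the point is a correction to the text, not a threat to the trial.

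A second reply is that one-sided testing was declared openly and in advance, and fits the directional hypothesis under Trial objective. That also stands as far as it goes. A pre-declared one-sided 5% test is a design choice and not an error in itself. A reader might infer that one-sided was plainly a slip for two-sided, or that the more lenient error rate was adopted without any reason. The document supports neither. The match with the two-sided result is strong evidence but does not prove which element is wrong, and the directional hypothesis is a reason of a kind.

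Third, 80 can be reached under one-sided testing by inflating for dropout twice: 51 / 0.8 gives 64, and 64 / 0.8 gives 80. The section names only one 20% allowance, so this would replace one inconsistency with another. The article states no clustering allowance or multiplicity adjustment that would account for the difference.

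Nor does the article format excuse the mismatch. The inputs and the result are both printed, and they disagree.

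**Conclusion.** The inconsistency is real and of moderate weight. For the one-sided test named, the stated inputs lead to 64 randomised per condition (128 in total), not 80 (160). For the N stated, one-sided power is about 0.88, not 0.80. The stated N and power agree with each other only for a two-sided test at 0.05. As a result it is unclear whether the primary comparison allows 5% or 2.5% error in favour of Grief-Help.

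The sample size and power figures assume an unadjusted two-group t-test, 1:1 allocation and a single 20% dropout allowance. The power figures are lower bounds for the planned ANCOVA in so far as the baseline score predicts the outcome. A reader might infer that the trial is too small, but the reverse is true: it is larger than the named test needs.

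**What to change.** State one sidedness in the Sample size section and use the same one for the primary analysis under Statistical analyses.

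**Preferred:** two-sided testing at alpha 0.05, with 64 analysed and 80 randomised per condition after 20% dropout, giving 80% power for d = 0.50 in an unadjusted comparison. All other stated figures then remain true and N stays at 160. The cost is one or two sentences and no extra children. Unadjusted power is about 0.80 where a one-sided test would have about 0.88, and the planned covariate recovers some of that difference.

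**If one-sided testing is really intended:** give the reason, and restate the power at 160 as about 88% (unadjusted).

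Either way, settle it before outcome data are analysed. Recruitment was still open when the article was written, and a choice of sidedness made after the results are seen could look data-driven.
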